
**Fig. 1 Fig1:**
[figure not shown]
Five guiding principles of Advanced Access model

Many studies have been conducted on advanced access in different countries, particularly the United States and the United Kingdom, which have shown positive impacts in terms of reduced wait time for the third available appointment [11–14], reduced missed appointments (no-shows) [13], and increased satisfaction among both professionals [15, 16] and patients [13]. Advanced access is becoming increasingly popular in Canada. However, despite its wide dissemination, a considerable variation in the implementation of the five guiding principles of this model has been observed. These variations in implementation can influence the observed impacts of advanced access, making it difficult to distinguish the impacts attributable to the model itself from those linked to the context and to differences in implementation level [14, 17]. Earlier research has focused primarily on the impacts of advanced access [12–14, 16, 18], and few studies have analyzed the implementation challenges [17, 19–21]. Nevertheless, very few studies to date provide an in-depth understanding of the contextual factors that explain these variations in implementation level, a field that remains largely unexplored.

### Study context

This model has been endorsed by several professional associations across Canada including the College of Family Physicians of Canada. In Quebec, advanced access was first introduced in 2012 and is at present widely promoted by the Quebec College of Family Physicians (CQMF), as well as by the Ministry of Health and Social Services (MHSS). Numerous training sessions have been put in place to support its adoption and dissemination at the provincial level reaching out more than 2000 health care providers and administrative staff (nurses, physicians, and administrative assistants). Over the past 4 years, the majority of family physicians, in close partnership with other professionals working in primary care settings, have implemented advanced access in their organization. We conducted the first two studies (2014, 2016) to understand the early experiences of implementing advanced access with the first adopters family physicians [7], as well as with the first university family medicine groups (UFMGs) who implemented it in Quebec [22]. Results showed not only a wide variation in its implementation levels, but also different combinations of its key guiding principles, among medical practices, as well as among professionals working within the same settings. Data did not allow us to differentiate and understand more deeply the influence of contextual factors on the implementation of the different guiding principles. To our knowledge, no Canadian studies have been conducted since advanced access has been implemented on a more systematic scale, among various primary care organizations. Despite that advanced access has been widely spread, the considerable implementation variations observed suggest disparities in timely access among the population. Thus, there is a need to better understand the underlying reasons for these implementation variations of advanced access and to assess their impact on the intended outcomes. The knowledge generated form this research will be useful to identify context-specific strategies to ensure a successful implementation of advanced access in primary care organizations and ultimately to improve timely access to care.

All UFMGs in Quebec are required to implement an advanced access model based on the five guiding principles. UFMGs are a core primary care model and training sites for all family medicine residents and many other health care professions. UFMGs are an exemplary setting that provides early exposure of future health professionals’ to best practices during their training program and are potentially conducive to implementing advanced access in their future practice [23]. Aside from the exploratory study [24] that we conducted, few studies has been identified on the impact of variations in advanced access implementation in various teaching settings [25]. We observed different models of implementation of advanced access by residents, ranging from a simple pairing/twinning (i.e., sharing a panel of patients between two residents) to the implementation of a joint care model with nurses or a subteam (teamlet) of professionals, in which the resident is included. The results also revealed a variety of implementation challenges faced by the organization itself, and many others faced specifically by residents (e.g., ensuring a balance between timely access and relational continuity of care) that warrant further investigation in larger-scale studies.

### Study objectives

The primary objective of this study is to assess the variation in the implementation of the five guiding principles of advanced access in UFMGs across Quebec and to better understand the influence of the contextual factors on this variation and also on outcomes. The specific research objectives are to:
Measure the variability in the implementation of the five guiding principles of advanced access across all UFMGs in Quebec and identify the contextual factors influencing the implementation of advanced access;Gain a deeper understanding of how the contextual, organizational and professional factors influence the implementation of advanced access in four UFMGs;Compare the outcome indicators of advanced access in four UFMGs with regards to its implementation levels (e.g. average wait time for the third appointment, average rate of missed appointments, relational continuity of the team, attendance rate at the UFMG).

### Literature review

Few studies have examined the factors that influence implementation of the guiding principles of advanced access. They have mainly measured the implementation of some guiding principles [17, 26, 27] (e.g., review of the appointments system) while overlooking other principles (e.g., integrating interdisciplinary practice) and the implementation context. Goodall et al. [26] measured the variation in guiding principles in 245 general medicine clinics in England, without considering the contextual factors that influenced their implementation, nor the impact of those variations in implementation levels on outcomes. Conducting further analyses to assess the implementation context and the impact of implementation variations on patients’ experiences was one of their recommendations. Within the same project, Salisbury et al. [28] complemented this analysis by comparing clinics that had implemented advanced access with those that had not, to determine the impact of implementation variations on wait times for obtaining an appointment, continuity of care, appointment availability, and workload. However, their study was limited to assessing the whole advanced access model without distinguishing among the different guiding principles. As part of the same project, Pope et al. [17], in a sample of eight clinics, attempted to understand and explain the variations in implementation levels of the guiding principles and their impact in terms of benefits for patients and reduction in the numbers of missed appointments. Nevertheless, without adopting any comprehensive conceptual framework, they were able to only identify a few factors (misunderstanding or poor knowledge of the advanced access model, confusion between advanced access and same-day access to appointments, external incentives, and informal organizational behaviour) to explain variations in the implementation of advance access. Pickin et al. [27] conducted an assessment among general physicians in Great Britain on the implementation of the guiding principles of advanced access and revealed a number of barriers to its implementation, such as lack of resources and time to make a change, and a resistant culture to changing practice. Only one study, conducted by VanDeusen et al. [10, 29] considered implementation context and attempted to measure variations in implementation of advanced access among different clinical settings and their impacts on patient outcomes. Within an overall assessment of the effectiveness of advanced access implementation on a national scale (United States), the authors measured the extent of implementation of advanced access in 78 primary and specialty care clinics. Adopting a multidimensional conceptual framework, they analyzed three categories of factors (management structure and processes, staff and team capacities, and clinic context in terms of logistics and physical space) associated with the implementation level and their impacts on wait times and patient satisfaction. Their analysis showed that, despite a wide variation in the implementation of the guiding principles across the primary and specialty care clinics, four factors (time devoted to managing change, clinical managerial support, feedback on team performance, level of knowledge/skills) were significant predictors of this implementation. Also, broader implementation of advanced access was associated with a statistically significant improvement in patient access (shorter wait times for clinic appointments in primary care, orthopedics, and urology) and a higher patient satisfaction [10].^.^ Their results highlight the importance of understanding the dynamics and the role of context in successful implementation [30].

## Methods

### Conceptual framework

The conceptual framework for this project builds primarily on the multilevel framework of Fleuren et al. [31], which presents different factors that could potentially influence the implementation of an innovation (see Fig. 2). Our framework considers various factors -sociopolitical, organizational, professional, related to advanced access that could influence the implementation effectiveness and impact, of advanced access (shorter wait times for appointments, reduced missed appointments, and increased relational continuity, attendance at the UFMG, and patient satisfaction). Ultimately, identifying the influential factors will help to adapt the implementation strategy of advanced access to the local context [31] and achieve the intended outcomes. Thus, *sociopolitical* factors refer to the sociocultural and political environment and to the characteristics of patients living in the community. ***Organizational*** factors relate to the primary care organizations in which the intervention is implemented, particularly in terms of coordination, organizational policies, and financial, human, and material resources. ***Professional*** factors refer to characteristics of those working in the organization and interacting with patients such as their field of practice and expertise (e.g., qualifications) [32], level of knowledge, willingness to comply, and sense of self-efficacy in conducting activities within implementation process, etc. They also incorporate the standards and values that play a significant role in the implementation process [33]. Factors related to the advanced access model include procedural clarity, observability of results, compatibility, completeness, and complexity.

**Fig. 2 Fig2:**
[figure not shown]
Conceptual framework

### Methods

This study will be based on an explanatory sequential design that includes phase 1:a ***quantitative survey*** (objective 1) conducted in all the UFMGs, and phase 2: a ***multiple case study*** (objectives 2 and 3) using mixed data [34]. Phase 1 will allow us to develop a comprehensive profile of the implementation levels of the five guiding principles of advanced access across the province; to assess the intra (among types of professionals, namely the physicians, nurses, and primary care nurse practitioners), and inter (across all UFMGs) implementation variability; and to analyze the factors influencing the implementation variation of advanced access within teaching organizations. Phase 2 will provide an in-depth analysis and explanation of the influence of the different factors on implementation, to assess the influence from the perspectives of key users of the model (professionals and patients); and lastly will enable the measurement of the intended outcomes of advanced access. The qualitative and quantitative components are thus complementary *(*see Fig. 3*)*.

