## Abstract

**Background:**

Timely access in primary health care is one of the key issues facing health systems. Among many interventions developed around the world, advanced access is the most highly recommended intervention designed specifically to improve timely access in primary care settings. Based on greater accessibility linked with patients’ relational continuity and informational continuity with a primary care professional or team, this organizational model aims to ensure that patients obtain access to healthcare services at a time and date convenient for them when needed regardless of urgency of demand. Its implementation requires a major organizational change based on reorganizing the practices of all the administrative staff and health professionals. In recent years, advanced access has largely been implemented in primary care organizations. However, despite its wide dissemination, we observe considerable variation in the implementation of the five guiding principles of this model across organizations, as well as among professionals working within the same organization.

The main objective of this study is to assess the variation in the implementation of the five guiding principles of advanced access in teaching primary healthcare clinics across Quebec and to better understand the influence of the contextual factors on this variation and on outcomes.

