##### Analysis

To respond to *objective 1* (assess the implementation of the five guiding principles of advanced access in the UFMGs), a score will be calculated for each principle, by type of respondent. Implementation scores will be assessed for each advanced access guiding principle by type of professional. Then, scores will be aggregated to produce group scores at the UFMG level for each of the above-mentioned principles. The median or average of all UFMGs’ score will be used as a threshold to determine the implementation categorization (e.g., strong/weak) of the advanced access for each principle. Descriptive analyses in terms of proportions, means, or standard deviations will be generated to determine the implementation scores of each principle and the factors influencing implementation. Multiple linear and logistic regression analyses will be performed using SAS 9.4 to determine the influence of different factors on implementation scores.

The Phase 1 results will be used to produce an implementation profile (e.g., strong/weak) of the UFMGs to guide the selection of the four cases which will be further analyzed in depth in Step 2.

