## Discussion

This study addresses an important need identified by key stakeholders on timely access. In Canada, only 43% of the population report that they can see a doctor or nurse the same day or the next day when needed. This result is the lowest of all 11 Commonwealth Fund countries [56]. In recent years, advanced access has been widely implemented in primary care organizations as a promising solution to reduce wait times. Its implementation requires a major organizational change based on redesigning the work process of all the administrative staff and health professionals. However, despite its wide dissemination, we observe considerable variation in the implementation of the five guiding principles of this model not only among organizations, but also among professionals working within the same organization. Several scientific articles have studied the impacts of advanced access, and some have analyzed its implementation. Nevertheless, very few studies provide an in-depth understanding of the factors that explain the variations of the implementation levels and their impact on outcomes. This study will make a novel contribution to the field of implementation science and will fill an important gap in the literature on implementing advanced access in teaching primary healthcare clinics.

The findings will enhance understanding of how and why some primary care settings ensure successful implementation of advanced access and reduce wait times while others present a gap of implementation and fail to satisfy their patients’ needs and preferences with regards to timely access. More specifically, they will help to clarify which specific component (or guiding principle) of this complex innovation or which combination of guiding principles are critical to implementation effectiveness and should be prioritized by key stakeholders in particular contexts and by decisions makers to reduce wait times.

Identifying factors associated with successful implementation and positive outcomes provides useful lessons for future implementation and diffusion of advanced access in Quebec and across all Canadian provinces.

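### Phase 1 narrows within-clinic variability to differences among professional types, and names no step that separates respondent noise from true differences between UFMGs

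*Protocol article*

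**What the plan says.** The within-clinic problem is described three times at the level of the individual professional. The Abstract (Background) reports variation across organizations, "as well as among professionals working within the same organization". Study context reports it from the team's earlier studies, "among medical practices, as well as among professionals working within the same settings". The Discussion repeats that it is seen "not only among organizations, but also among professionals working within the same organization".

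Specific objective 1 (Study objectives) is to "Measure the variability in the implementation of the five guiding principles of advanced access across all UFMGs in Quebec"; it names no within-clinic component. The Methods section then gives the working definition: Phase 1 is "to assess the intra (among types of professionals, namely the physicians, nurses, and primary care nurse practitioners), and inter (across all UFMGs) implementation variability".

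The Step 1 Analysis follows that definition. Each principle is first scored separately for every professional type. The next step reads: "Then, scores will be aggregated to produce group scores at the UFMG level for each of the above-mentioned principles". Clinics are afterwards labelled, for instance as strong or weak, by a cut at the centre of the clinic scores, either mean or median. The other tools named are means, proportions and SDs, at no stated level, and linear and logistic regression. Multilevel models appear only in the Step 2 quantitative analysis, where nesting within UFMGs is the reason given for them.

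**The concern.** Differences among types and differences among individuals of one clinic are not the same quantity. An average UFMG has about 20 physicians. How far they differ from one another is part of the problem as described, but a comparison of physicians with nurses and nurse practitioners does not show it. Residents are also surveyed (Participant recruitment), yet they are not among the three types in the definition.

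The second issue follows from the first. Differences among individuals that are averaged into a clinic score remain in that score as sampling error. If the spread of up to 47 such scores is reported as the variability across UFMGs, part of it is respondent noise. The main objective is to assess variation in implementation, so the size and level of that variation is the result a reader will look for. Step 1 respondents are nested in UFMGs just as the Step 2 data are, but the Step 1 text names no method that uses this.

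**Working it through.** The article states no variance or ICC, so it has no figure of its own to reproduce here. Its power figures (94.9% and 82%) come without a test or effect size and are not used below.

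**Inputs from the article**
- Average staff per UFMG: 20 physicians, 18 residents, 2 nurse clinicians, 1 primary care nurse practitioner, total 41 (Step 2, quantitative data collection).
- Response rates said to be needed: 25% for physicians and residents, 40% for nurses and nurse practitioners (Participant recruitment).
- Totals: about 980 physicians, 80 nurse clinicians, 90 nurse practitioners in 47 UFMGs (Participant recruitment).

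**Assumed, because the article gives none:** an ICC of 0.05 to 0.30, and a gap between physicians and the other two types of 0.2 to 0.8 within-type SD.

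**Between-UFMG spread.** Respondents per UFMG: n = 0.25 × 38 + 0.40 × 3 = 9.5 + 1.2 = 10.7. With total respondent variance set to 1, the variance of a raw clinic mean is ICC + (1 − ICC)/n.
- Noise share = [(1 − ICC)/n] / [ICC + (1 − ICC)/n].
- SD factor = √{[ICC + (1 − ICC)/n] / ICC}.
- If the target is the mean of the clinic's actual 41 staff, the divisor becomes ICC + (1 − ICC)/41.

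| Assumed ICC | Noise share | SD factor | SD factor, actual-staff target |
|---|---|---|---|
| 0.05 | 64% | 1.67 | 1.38 |
| 0.10 | 46% | 1.36 | 1.23 |
| 0.20 | 27% | 1.17 | 1.12 |
| 0.30 | 18% | 1.10 | 1.07 |

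Example at ICC 0.10: 0.90/10.7 = 0.084; √(0.184/0.10) = 1.36; with 0.90/41 = 0.022, √(0.184/0.122) = 1.23.

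For a physician score alone, n = 0.25 × 980/47 = 5.2, and the first SD factor becomes 2.2, 1.65, 1.33 and 1.20 in the same order.

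A simulation of 47 clinics with 245 respondents confirms that the excess can be removed. At true ICC 0.10 the raw variance of clinic means averaged 0.325, while the variance-components estimate averaged 0.10. At true ICC 0 the figures were 0.247 and about 0.

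**Within-clinic spread.** Let p be the share of staff who are nurses or nurse practitioners, and d their common distance from physicians in within-type SD. The between-type share of within-clinic variance is p(1 − p)d² / [p(1 − p)d² + 1].
- Staff mix 20/2/1: p = 3/23, p(1 − p) = 0.113. For d = 0.2, 0.5, 0.8 the share is 0.5%, 2.8%, 6.8%.
- Survey totals 980/80/90: p = 170/1150, p(1 − p) = 0.126. The share is 0.5%, 3.1%, 7.5%.

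Under these assumptions most of the within-clinic variance lies inside types.

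**Can types be compared within one clinic?** Expected respondents per UFMG are 0.40 × 80/47 = 0.68 nurse clinicians and 0.40 × 90/47 = 0.77 nurse practitioners. If responses fall at random (Poisson), 47 × e^(−0.68) ≈ 24 clinics have no nurse clinician and 47 × e^(−0.77) ≈ 22 have no nurse practitioner. Type differences are therefore better estimated across clinics in one model than clinic by clinic.

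**The case against.** The operational plan is consistent with itself: objective 1 names variability across UFMGs, the Methods section openly defines the within-clinic part by type, and the Step 1 Analysis scores by type to match. The individual-level wording stands in the background and discussion. This holds, and it is why the point is a narrowing of scope. A reader might infer that the plan misses a figure promised in its primary objective; Study objectives does not support that.

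Nor does any sentence say that the SD of the aggregated scores will be the between-UFMG result. The SDs have no stated level and could describe respondents of one type, and the exact estimator may stand in a fuller document. The aggregated scores are explicitly used for the strong or weak label and for profiles. The overstatement is therefore conditional on the natural reading.

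The size is also open to challenge. Every factor rests on an assumed ICC. The response rates are those said to be needed, not predicted, and a higher response would reduce the noise. Because all professionals are invited, the mean of the actual staff is a legitimate target, and it lowers the factors. The directors' survey, which also measures implementation, is not in the noise model. All of this bears on size. The direction stands whenever the ICC is below 1 and response is incomplete.

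Two stronger readings should be set aside. One is that the study will wrongly attribute variation to the clinic instead of the individual: the article plans no weighing of intra against inter variance, and a type comparison would report mean differences, not a variance share. The other is that the four cases will be wrongly chosen: they are picked from high and low scores and also by geography and size, and the figures here show no selection error for that step.

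**Conclusion.** The concern holds in a limited form. The study describes variation among professionals within one organization, while Phase 1 defines and scores only differences among types, so no within-clinic, within-type figure is planned. If between-UFMG variability is taken from the spread of aggregated scores, it will be too large: by about 1.1 to 1.7 times on the SD scale at 10.7 respondents per UFMG, or about 1.07 to 1.4 times against the clinic's actual staff. The lower ends belong to an assumed ICC of 0.30 and the upper ends to 0.05. The direction does not depend on the ICC; the size does. The matter is worth correcting because variation in implementation is what the study sets out to assess, and the individual scores needed to do so will already be in hand.

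**What to change.** In the Methods section, define intra-UFMG variability as variation among individual professionals of the same UFMG, with professional type as one component and the surveyed residents included among the types.

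In the Step 1 Analysis, fit for each principle a mixed model to the individual professionals' scores, with a fixed effect for type and a random UFMG intercept. Report the between-UFMG SD, the within-UFMG within-type SD, the type differences and the ICC, with confidence intervals. State the level of any other SD reported. Model-based (shrunken) UFMG scores may be shown beside the raw scores when clinics are profiled.

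The cost is slightly more analysis work, a few lines in the SAS software already planned, and no new data. The reported between-UFMG variation will be smaller than the raw spread.
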